## Abstract

**Background:**

Any metal placed in a biological environment undergoes corrosion. Thus, with their large metallic surfaces, TKA implants are particularly prone to corrosion with subsequent release of metal ions into the human body which may cause local and systemic toxic effects and hypersensitivity reactions, and increase cancer risk. To address this problem, a new 7-layer zirconium coating developed especially for cobalt-chrome orthopaedic implants was tested biomechanically and found to lower metal ion release.

The purpose of the proposed clinical trial is to compare the metal ion concentration in patients' plasma before and after implantation of a coated or uncoated TKA implant.

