**Methods/Design:**

In this randomised controlled trial, 120 patients undergoing primary TKA will be recruited at the Department of Orthopaedic Surgery of the University Hospital in Dresden, Germany, and randomised to either the coated or uncoated prosthesis. Outcome assessments will be conducted preoperatively and at 3 months, 12 months and 5 years postoperatively. The primary clinical endpoint will be the chromium ion concentration in the patient's plasma after 1 and 5 years. Secondary outcomes include cobalt, molybdenum and nickel ion concentrations after 1 and 5 years, allergy testing for hypersensitivity against one of these metals, the Knee Society Score to assess clinical and physical function of the knee joint, the self-assessment Oxford Score and the Short Form 36 quality of live questionnaire.

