### Study Hypothesis

The study's hypothesis is that metal ion concentrations in the patient's plasma will be significantly lower in the group receiving the ZrN-coated implant than in the other group.

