### Inclusion and Exclusion Criteria

Potential participants will be screened and recruited at the orthopaedic pre-admission clinic.

Inclusion criteria are: (i) indication for TKA in cases of primary or secondary osteoarthritis, (ii) written informed consent. Exclusion criteria include (i) metal implants or endoprostheses, (ii) hypersensitivity against metals or bone cement particles, (iii) any form of malignancies, (iiii) renal insufficiency, (iiiii) other severe illnesses that would impair participation in this study. All eligible patients will be asked whether they are willing to participate in the trial and, if so, required to provide a written informed consent. They will be informed about the purpose of the trial, the operative procedures as well as their options and risks. They will be randomised to either a coated or uncoated TKA implant (Columbus, Aesculap, Tuttlingen, Germany, see figure 1 & 2) using a randomisation list.

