### Clinical Endpoints

The primary endpoint of this investigation is the difference in chromium ion concentration in the patient's plasma after 1 and 5 years. Secondary endpoints are the differences in cobalt, molybdenum and nickel ion concentration after 1 and 5 years and a possible hypersensitivity against one of these metals after 1 year postoperatively.

The metal ion concentrations are to be analysed for a potential correlation to biomechanical factors (BMI, mechanical axis), activity (UCLA), function (KSS) and quality of live (Oxford Score, SF 36).

The patients will be clinically examined preoperatively and 3 months, 1 year and 5 years after surgery. They will be asked to complete the Knee Society score, the Oxford Knee score, the Short Form 36 and the UCLA activity score questionnaires. They will be tested for hypersensitivity against metal ions preoperatively and one year postoperatively. They will be contacted by phone 2, 3 and 4 years postoperatively and asked to complete the Oxford Knee score questionnaire. Adverse and serious adverse events will be evaluated according to Good Clinical Practice (see table 1 for details).

**Table 1 T1:** Summary of the study parameters

	**Preop**.	**Discharge** **7 - 10 days** **postop**.	**Follow-up** **3** **months**	**Follow-up** **12 months**	**Follow-up** **2 years**	**Follow-up** **3 years**	**Follow-up** **4 years**	**Follow-up** **5 years**
Clinical examination	**X**		**X**	**X**				**X**
Contact by phone					**X**	**X**	**X**	
Metal ion concentrations in plasma	**X**			**X**				**X**
Testing for hypersensitivity	**X**							**X**
Knee Society score	**X**		**X**	**X**				**X**
Oxford score	**X**		**X**	**X**	**X**	**X**	**X**	**X**
UCLA activity score	**X**		**X**	**X**				**X**
SF 36	**X**		**X**	**X**				**X**
AE/SAE		**X**	**X**	**X**	**X**	**X**	**X**	**X**

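### The stated before/after purpose does not match the between-arm primary endpoint; align the wording and adjust for the preoperative chromium value already collected

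*Protocol article*

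**What the plan says.** The protocol article describes the primary comparison in four places.

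- **Abstract, Background (purpose):** to "compare the metal ion concentration in patients' plasma before and after implantation of a coated or uncoated TKA implant".
- **Abstract, Methods/Design (primary endpoint):** "The primary clinical endpoint will be the chromium ion concentration in the patient's plasma after 1 and 5 years".
- **Clinical Endpoints (primary endpoint):** "the difference in chromium ion concentration in the patient's plasma after 1 and 5 years". The reference for the difference is not given.
- **Study Hypothesis:** "metal ion concentrations in the patient's plasma will be significantly lower in the group receiving the ZrN-coated implant than in the other group".

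The last paragraph of the main Background section also states the aim as a comparison of the coating with the standard alloy. Sample Size Considerations starts from a postoperative chromium level in patients with an uncoated implant. In Table 1 the row "Metal ion concentrations in plasma" is marked preoperatively, at 12 months and at 5 years.

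**The concern.** A reader cannot tell from the endpoint wording alone what the preoperative sample is for. The purpose sentence suggests either a within-arm before/after comparison or a change score. The hypothesis suggests a comparison of postoperative levels between arms. The Clinical Endpoints wording could be read as a difference between arms, from baseline, or between years 1 and 5.

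Two of these readings would not answer the hypothesis. A within-arm before/after comparison does not estimate the effect of the coating, and a year-1-to-year-5 difference is another quantity altogether. A change score does address the coating effect, but it can be less precise than ignoring the baseline. A comparison of raw postoperative levels leaves the baseline information unused, and any chance imbalance in background chromium stays in the estimate, with about 45 evaluable patients per arm.

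**Working it through.** **1. The passages side by side.** The hypothesis, the aim and the sample size all point to coated versus uncoated postoperative levels. The abstract's endpoint names the same measured variable without the comparison. The Clinical Endpoints wording fits that comparison but does not state it. The abstract's purpose sentence is the outlier. None of these places uses the preoperative value.

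**2. The plan's own figure.** Sample Size Considerations gives 60 per group at 5% significance, 80% power and 25% drop-out, so 60 × 0.75 = 45 evaluable per group. Inputs there: 0.92 µg/l, interquartile range 0.73–1.32, 40-fold in-vitro ratio.

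- SD ≈ (1.32 − 0.73)/1.349 = 0.437 (normal approximation).
- Difference = 0.92 − 0.92/40 = 0.897.
- n = 2 × (0.437 × 2.80/0.897)² ≈ 3.7, so 4 per group (two-sided test assumed).
- Dividing by 0.864 for a rank test gives 5; 5/0.75 gives 7 enrolled.

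The stated 60 is not reproduced. That is a separate matter, but it means that the 80% below is a nominal starting point. Working backwards, 45 per group has 80% power for 0.437 × √(2/45) × 2.80 = 0.258 µg/l, which is 28% of 0.92.

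**3. Variance relative to comparing postoperative levels.** Let r be the correlation of preoperative and postoperative values, with equal SDs at both times.

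- Baseline-adjusted comparison (ANCOVA): 1 − r².
- Change score: 2(1 − r).
- Power = Φ(2.80/√factor − 1.96).

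| r (assumed) | ANCOVA factor | ANCOVA power | Change-score factor | Change-score power |
|---|---|---|---|---|
| 0.1 | 0.99 | 80.4% | 1.80 | 55% |
| 0.3 | 0.91 | 83.6% | 1.40 | 66% |
| 0.5 | 0.75 | 89.9% | 1.00 | 80% |

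The change score is less precise than ignoring baseline whenever r < 0.5. The adjusted comparison is at least as precise as the change score at every r, because 2(1 − r) − (1 − r²) = (1 − r)² ≥ 0. Asymptotically it is never less precise than comparing levels.

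**4. Effect of the detection limit.** Metal Ion Analysis gives a limit of 0.5 µg/l and moves lower values to below 0.25 µg/l. Patients with "metal implants or endoprostheses" are excluded, so many preoperative values may be non-detects (an inference; no baseline distribution is given). A simulation used lognormal values with log-SD ln(1.32/0.73)/1.349 = 0.439 and a postoperative median of 0.92, setting values below 0.5 to 0.25.

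| True r | Preoperative non-detects | Observed r | 1 − r² | Power by the formula in step 3 |
|---|---|---|---|---|
| 0.5 | 80% | 0.34 | 0.884 | about 85% |
| 0.5 | 95% | 0.22 | 0.952 | about 82% |
| 0.3 | 80% | 0.21 | 0.958 | about 82% |
| 0.3 | 95% | 0.13 | 0.982 | about 81% |

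In patients, the saving is 45 − 45(1 − r²), rounded down: 5 and 2 of 45 per group in the first two rows, 1 and 0 in the last two.

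**The case against.** The strongest reply is that the intent is already clear. The hypothesis and the aim are between-arm, and in a two-arm trial a difference in the endpoint most naturally means a difference between arms. The purpose sentence may simply describe the sampling schedule. Much of this stands: the mismatch is a matter of clarity and does not undermine the design.

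A reader might infer more than the document supports in four ways.

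- **That the covariate settles the estimand.** It does not. Under randomisation the between-arm mean difference in level, in change and from linear ANCOVA is the same quantity. The covariate changes precision; only the wording can fix the target. Nor does it settle the choice between 1 and 5 years.
- **That the absence of an analysis model is a defect.** A condensed article commonly leaves covariates, scale and non-detects to the full protocol or analysis plan, which are not shown.
- **That the choice is being held open until the 1-year data are seen.** Data Acquisition and Management plans an interim analysis at that point, but nothing says the analysis is undecided.
- **That power is at risk.** At the plan's own in-vitro effect, 45 per arm has power of about 100%, and the document never specifies a change score. The figures above compare methods; they do not show harm done.

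What remains is that the purpose and endpoint statements do not agree, that the reference for the difference is missing, and that a scheduled sample has no stated use in the primary comparison. Defining the primary endpoint consistently is the protocol's own task.

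**Conclusion.** The point holds as an inconsistency of wording with a useful, inexpensive remedy. The before/after purpose does not match the postoperative, between-arm endpoint and hypothesis, and the preoperative chromium value is collected without a role in any of them.

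The benefit of adjustment is conditional. From a nominal 80%, it runs from nothing noticeable (r = 0.1) to about 10 percentage points (r = 0.5), and preoperative non-detects may push it to the low end. Taking the purpose sentence as a change score would lower power by about 25 points at r = 0.1 and 14 at r = 0.3, and leave it unchanged at r = 0.5. These figures rest on assumed correlations, a two-sided 5% test and, for the change score, equal SDs before and after surgery. Confidence is medium: the mismatch can be read directly from the text, while the size of the gain cannot be known from it.

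**What to change.** Bring the abstract's purpose sentence, the abstract's endpoint sentence and the Clinical Endpoints section into line with the Study Hypothesis. The primary quantity is the coated-versus-uncoated comparison of postoperative plasma chromium, adjusted for each patient's preoperative chromium. Say that it is neither a within-arm before/after comparison nor a change score. Use the same form for cobalt, molybdenum and nickel.

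The analysis plan can choose the scale and the treatment of non-detects, including those in the preoperative covariate. The change should be in place before the 1-year analysis.

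The cost is a few sentences, plus that modelling decision in the analysis plan. No extra sample, visit or patient is needed, since Table 1 already schedules the preoperative sample.

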**Methods/Design:**

In this randomised controlled trial, 120 patients undergoing primary TKA will be recruited at the Department of Orthopaedic Surgery of the University Hospital in Dresden, Germany, and randomised to either the coated or uncoated prosthesis. Outcome assessments will be conducted preoperatively and at 3 months, 12 months and 5 years postoperatively. The primary clinical endpoint will be the chromium ion concentration in the patient's plasma after 1 and 5 years. Secondary outcomes include cobalt, molybdenum and nickel ion concentrations after 1 and 5 years, allergy testing for hypersensitivity against one of these metals, the Knee Society Score to assess clinical and physical function of the knee joint, the self-assessment Oxford Score and the Short Form 36 quality of live questionnaire.

**Discussion:**

The metal ion concentration in the patient's plasma has been shown to increase after TKA, its eventual adverse effects being widely debated. In the light of this discussion, ways to reduce metal ion release from orthopaedic implants should be studied in detail. The results of this investigation may lead to a new method to achieve this goal.

**Trials register:**

Clinicaltrials registry NCT00862511

## Background

Total knee arthroplasty (TKA) is a very successful treatment option for advanced osteoarthritis of the knee with about 146.000 operations performed in 2008 in Germany [1]. Although patients obviously benefit from joint replacement in terms of mobility and quality of life, implant-specific local and systemic adverse effects, due to corrosion and wear, still constitute a matter of concern [2-6]. Besides polyethylene wear which is one cause for aseptic loosening, metal ion release from metallic implants is also subject of debate. Every metal implant in a biological environment corrodes, depending on the exposed surface area and the composition of the alloy [7]. This process results in the release of metal ions.

It has been suggested that metal ion release may trigger local and systemic toxic effects [8] and hypersensitivity reactions [9-12]. Furthermore, in animal studies, cobalt and chromium ion exposure was found to have carcinogenic and mutagenic effects. Therefore, cancer risk may increase from exposure to the cobalt and chromium ions released by metal implants [13-15]. In contrast to these experimental data, epidemiologic studies did not find a greater risk of developing a malignancy after TKA [6,16,17]. However, increases in lymphoma, cancer of the endometriuma and prostate and skin melanoma were observed that could be related to TKA [16,17].

As they contain large metallic surfaces, TKA implants are particularly subject to corrosion inducing release of metal ions. Significantly higher metal ion concentrations were detected in patients after TKA compared to patients without metal implants [18]. Attempts have been made to reduce metal ion release and to improve the tribological properties of TKA implants by coating the chrome-cobalt body with various zirconium compositions, especially designed for patients with metal hypersensitivity. In in-vitro biomechnical tests, they showed superior tribological characteristics and thus less polyethylene wear particles [19-22]. However, in clinical tests, they presented early radiolucent lines [23] and achieved less favourable results in the Australian TKA registry [24].

To reduce ion release, a new multilayer coating system was developed consisting of a thin adhesive chrome layer, five alternating intermediate layers out of chrome nitride (CrN)-chrome carbonitride (CrCN) and a final shielding zirconium nitride (ZrN) layer.

The 7-layer coating system is applied on the CoCrMo knee implants through the chemical vapour deposition (CVD) method with a total thickness of about 3,5 to 6 μm. The gradiently applied CrN-CrCN layers allow to bridge the difference in hardness and tension between the softer material CoCrMo and the very hard ZrN shielding layer and thus ensure the system's mechanical integrity. The interfaces between the layers constitute an additional diffusion barrier against ions from the base material. In addition, the final ceramic ZrN layer seals the system and is highly biocompatible.

To evaluate its abrasive properties, it was tested in an in-vitro simulation according to ISO 14243-1:2002(E) through 5 million cycles with a frequency of 1 Hz.

Nickel and molybdenum ion release of the ZrN-coated implants into the wear test serum was reduced to the point that traces of these elements were found only within the range of detection levels while only minimal traces of cobalt and chrome were detected in the test serums, inferior by orders of magnitude to those of the uncoated implants out of CoCrMo [25].

Therefore, this surface coating could help to significantly reduce release of metal ions in TKA patients.

The aim of this study is to compare this novel surface coating with the standard CrCoMb-alloy in terms of metal ion levels in patients' plasma, metal hypersensitivity and clinical and radiological results.

### Study Hypothesis

The study's hypothesis is that metal ion concentrations in the patient's plasma will be significantly lower in the group receiving the ZrN-coated implant than in the other group.

## Methods/Design

This study is a single-centre randomised controlled trial that will be conducted at the Medical Faculty of the Technical University of Dresden. The study protocol was approved by the local independent Ethics Committee in February 2009 and registered in the US National Institutes of Health's database  registry under NCT00862511.

The trial is performed according to the guidelines for Good Clinical Practice (GCP), as applicable.

### Inclusion and Exclusion Criteria

Potential participants will be screened and recruited at the orthopaedic pre-admission clinic.

Inclusion criteria are: (i) indication for TKA in cases of primary or secondary osteoarthritis, (ii) written informed consent. Exclusion criteria include (i) metal implants or endoprostheses, (ii) hypersensitivity against metals or bone cement particles, (iii) any form of malignancies, (iiii) renal insufficiency, (iiiii) other severe illnesses that would impair participation in this study. All eligible patients will be asked whether they are willing to participate in the trial and, if so, required to provide a written informed consent. They will be informed about the purpose of the trial, the operative procedures as well as their options and risks. They will be randomised to either a coated or uncoated TKA implant (Columbus, Aesculap, Tuttlingen, Germany, see figure 1 & 2) using a randomisation list.

**Figure 1 F1:**
[figure not shown]
**View of the Columbus knee system (Aesculap, Tuttlingen, Germany)**.

**Figure 2 F2:**
[figure not shown]
**View of the the ZrN-coated Columbus AS knee system (Aesculap, Tuttlingen, Germany)**.

### Operative Procedure

In all cases, the coated or uncoated model of a cemented unconstrained total knee prosthesis with a fixed polyethylene insert is implanted. Both implants are CE-certified.

All operations are performed with a tourniquet after a single dose of antibiotics (1.5 g Cefuroxim), using a medial parapatellar approach with a femur-first preparation.

Femoral alignment in the frontal plane is is directed at an angle of 90° to the mechanical axis in the frontal plane. For sagittal alignment, it is placed parallel to the ventral femoral cortex and, for rotational alignment, parallel to the transepicondylar axis. Tibial alignment is directed at an angle of 90° to the mechanical axis in the frontal plane, with a 5° posterior slope in the sagittal plane and at the medial third of the tibial tubercle for rotational alignment. Postoperatively full weight-bearing is allowed, and mobilisation starts from the first postoperative day.

### Clinical Endpoints

The primary endpoint of this investigation is the difference in chromium ion concentration in the patient's plasma after 1 and 5 years. Secondary endpoints are the differences in cobalt, molybdenum and nickel ion concentration after 1 and 5 years and a possible hypersensitivity against one of these metals after 1 year postoperatively.

The metal ion concentrations are to be analysed for a potential correlation to biomechanical factors (BMI, mechanical axis), activity (UCLA), function (KSS) and quality of live (Oxford Score, SF 36).

The patients will be clinically examined preoperatively and 3 months, 1 year and 5 years after surgery. They will be asked to complete the Knee Society score, the Oxford Knee score, the Short Form 36 and the UCLA activity score questionnaires. They will be tested for hypersensitivity against metal ions preoperatively and one year postoperatively. They will be contacted by phone 2, 3 and 4 years postoperatively and asked to complete the Oxford Knee score questionnaire. Adverse and serious adverse events will be evaluated according to Good Clinical Practice (see table 1 for details).

**Table 1 T1:** Summary of the study parameters

	**Preop**.	**Discharge** **7 - 10 days** **postop**.	**Follow-up** **3** **months**	**Follow-up** **12 months**	**Follow-up** **2 years**	**Follow-up** **3 years**	**Follow-up** **4 years**	**Follow-up** **5 years**
Clinical examination	**X**		**X**	**X**				**X**
Contact by phone					**X**	**X**	**X**	
Metal ion concentrations in plasma	**X**			**X**				**X**
Testing for hypersensitivity	**X**							**X**
Knee Society score	**X**		**X**	**X**				**X**
Oxford score	**X**		**X**	**X**	**X**	**X**	**X**	**X**
UCLA activity score	**X**		**X**	**X**				**X**
SF 36	**X**		**X**	**X**				**X**
AE/SAE		**X**	**X**	**X**	**X**	**X**	**X**	**X**

### Metal Ion Analysis

Blood samples are collected in 7,5 ml S-Monovette^® ^tubes (for trace metal analysis, Sarstedt AG, Germany) using a specific steel needle for trace metal analysis (Sarstedt AG, Germany). Within one hour, plasma is separated by centrifugation at 2000 g for 10 min. Samples are stored at -20°C before being analysed for chromium, cobalt, molybdenum and nickel content using a graphite furnace atomic absorption spectrometer Z-8270 with Polarisation-Zeeman-Absorption (Hitachi Ltd., Japan) [26,27]. Calibration is performed by the standard addition method using 0.00 μg/l, 5.00 μg/l and 10.00 μg/l as calibration points in triplicate for each element. The samples are diluted 1:2 in buffer (1% HNO_3 _[Merck AG, Germany], 0.2% Triton X-100 [SIGMA-Aldrich Chemie GmbH, Germany], 0.2% Antifoam B [SIGMA-Aldrich Chemie GmbH, Germany]; Cr and Co: additional 0.8% Pd-matrix-modifier [Merck AG, Germany], 0.3% Mg-matrix-modifier [Merck AG, Germany]). The accuracy and precision of the method is validated to < 10% using the control materials Seronorm™ Trace Elements Serum (SERO AS, Norway). The detection limit of the method is estimated at 0.5 μg/l for each element (mean +3sd from buffer). The Dixon test was used to eliminate aberrant values. All probes having ion levels below the detection levels are adjusted to <0.25 μg/l.

